### Statistical data analysis

#### Sample size calculation

The sample size was calculated using the McNemar’s test^16^ for paired proportions, informed by the comparison of pathogen yield from paired induced sputum and six-lobe FB-BAL samples in the CF-SPIT study.^15^ Assuming a proportion of discordant pairs of 0.37 we require a sample size of 110 to detect a ratio of discordant proportions (identification of an organism(s) on FB-BAL not isolated on induced sputum vs identification of organism(s) on induced sputum not identified on FB-BAL) of 3, with 90% power and 0.05 significance. If we assume the same induced sputum success rate as CF-SPIT (84%), we need a final sample size of 131. The sample size required to detect a difference between cough swab and FB-BAL is smaller due to a higher proportion of discordant pairs.

#### Primary outcome analysis

The organisms isolated from each participants cough swab will be compared with those isolated from their FB-BAL samples to identify concordance/discordance. The pathogen yield is concordant if the same organism(s) are identified in both samples or no organisms are identified in either. If the same organisms are not identified in both samples the pathogen yield is discordant. Discordance will be classified as CS^+^/FB-BAL^−^ when an organism is isolated on cough swab but not on FB-BAL or CS^−^/FB-BAL^+^ when an organism is isolated on FB-BAL but not on cough swab. This will be repeated with the FB-BAL organisms limited to those from a single lobe (RML) and two lobes (RML and LLi) to allow comparison of pathogen yield if a more limited FB-BAL sampling methodology had been used. The same analysis will be undertaken to identify concordance/discordance between the induced sputum and the FB-BAL samples.

We will use conditional logistic regression analyses to estimate the OR of discordant proportions for the paired cough swabs and FB-BAL samples (identification of an organism(s) on FB-BAL not isolated on cough swab vs identification of organism(s) on cough swab not identified on FB-BAL). This will be analysed separately using FB-BAL results from one, two and six lobes. A similar analysis will be undertaken for the paired induced sputum and FB-BAL samples.

#### Secondary outcomes analysis

We will estimate the sensitivity for each sampling technique against a combined gold standard consisting of all pathogens isolated from the triplicate samples (cough swab, sputum induction and six-lobe FB-BAL). A positive outcome will be defined as the ability of a single technique to identify all pathogens from the combined gold standard. This will enable us to quantify the ability of each technique to correctly detect all lower airway pathogens in any given patient. Two-sided 95% score CIs for sensitivity will be estimated.We will use a logistic regression analysis to assess the effect of age on pathogen positivity and the success rate of sputum induction.The Likert score for tolerability will be summarised using a frequency table stratified for age.

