### Objectives

The primary objective is the discordance in pathogen yield between cough swab/induced sputum and FB-BAL.

The secondary objectives are as follows:

To calculate the sensitivity of each sampling technique (cough swab, induced sputum and FB-BAL) to correctly identify all pathogens isolated from the lower airway in children with PBB.To report the success rate of obtaining a usable induced sputum sample in children with PBB.To report the tolerability of the three sampling measures (cough swab, induced sputum and FB-BAL).

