#### Cough swab

The child will be instructed to tilt their head back and open their mouth wide. A sterile cotton swab will be placed at the back of the throat under the uvula and the child will be asked to cough. If the patient is too young to cough on command, the swab will be gently placed against the posterior pharynx to stimulate a cough. The sample will be labelled according to local guidelines and sent to the local microbiology.

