#### Induced sputum

A 8 mL of 7% saline will be administered through a disposable oxygen-driven jet nebuliser set at a flow rate of 5 L/min for 15 min. Chest physiotherapy appropriate to the child’s age and ability to cooperate will be given during and after the nebulised therapy. Oropharyngeal suction will be used to obtain a sputum sample if the child is unable to spontaneously expectorate. The sample will be labelled according to local guidelines and sent to the local microbiology laboratory for culture. Oxygen saturations (SpO_2_) will be monitored before, during and after procedure. If the child develops wheeze or SpO_2_ drops<94%, inhaled or nebulised salbutamol will be delivered. The procedure will be discontinued if symptoms persist or SpO_2_ remains <94%.

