#### FB-BAL

The FB-BAL is clinically indicated and will be performed as per standard of care and is therefore not a research procedure. It will be performed under general anaesthetic using the following methodology across all four sites. Once the bronchoscope is inserted, suction of secretions will be avoided before BAL to limit contamination with upper airway organisms. A single 10 mL aliquot lavage will be instilled and retrieved using a syringe attached to the bronchoscope channel in each of the six lobes (including lingula). The lavages will be undertaken in a specific order: right upper lobe, right middle lobe (RML), right lower lobe (RLL), left upper lobe, left lingular (LLi) and left lower lobe). The sample will be labelled according to local guidelines and sent to the local microbiology laboratory for culture.

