## Discussion

CLASSIC PBB will compare the pathogen yield from different lower airway sampling strategies in children with PBB. If either cough swab or induced sputum are shown to be useful alternatives to FB-BAL, it will enable more children with PBB to have the causative pathogen identified and therefore be prescribed targeted antibiotics. It would also reduce the need for FB-BAL in this condition which would be beneficial to children and their families due to the associated burden.

Cough swabs and induced sputum samples are not used routinely in children with PBB. They are, however, widely used in children with other respiratory illnesses who are unable to expectorate sputum. At UK paediatric CF) Centres, a cough swab is obtained at each out-patient appointment (2–3 monthly) as part of routine microbiological surveillance.^17^ They are easy to perform and well tolerated. The CF-SPIT study compared pathogen yield from cough swab, induced sputum and FB-BAL samples in children aged 6 months to 18 years with CF. They reported 69% of pathogens isolated at FB-BAL had been identified in cough swabs over the previous 12 months but a single cough swab was not representative of lower airway microbiology in CF. This supports the findings of a previous study which found the sensitivity of a single cough swabs to be 44% when compared with FB-BAL samples.^18^

Induced sputum has been shown to be a simple, cost effective, well tolerated and repeatable method of sampling the lower airway in children with CF.^15 19^ In the CF-SPIT study, the pathogen yield of 41 paired induced sputum and FB-BAL samples was compared.^15^ Of the 41 paired samples, 28 (68%) had a positive growth from at least one of the samples with 39 pathogens isolated in total. Induced sputum identified 27 (69%) pathogens, single-lobe FB-BAL identified 22 (56%), two-lobe FB-BAL 28 (72%) and six-lobe FB-BAL identified 33 (85%). Importantly, some pathogens were isolated from induced sputum and not FB-BAL reflecting the relative inability of FB-BAL to sample the larger airways. The authors of the CF-SPIT concluded that in children with CF, sputum induction is a credible surrogate for BAL and a substantial number of FB-BALs could be avoided if sputum induction is done first and pathogens appropriately treated.^15^

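### The secondary sensitivity analysis scores each technique against a reference that contains its own result and counts throat-swab-only organisms as lower-airway pathogens, so it measures relative yield rather than sensitivity

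*Protocol article*

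**What the plan says.** All references are to the Protocol article.

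- **Target.** Under Objectives, each technique is to be assessed on its ability "to correctly identify all pathogens isolated from the lower airway in children with PBB".
- **Reference.** Under Outcomes and again under Secondary outcomes analysis, the reference is the union of the three samples: a "combined gold standard consisting of all pathogens isolated from the triplicate samples (cough swab, sputum induction and six-lobe FB-BAL").
- **Scoring rule.** "A positive outcome will be defined as the ability of a single technique to identify all pathogens from the combined gold standard".
- **Interpretation.** The section says this quantifies how well each technique can "correctly detect all lower airway pathogens in any given patient".
- **How the samples are taken.** The cough swab is held at the back of the throat. For a child too young to cough on command, "the swab will be gently placed against the posterior pharynx to stimulate a cough". For induced sputum, "Oropharyngeal suction will be used to obtain a sputum sample if the child is unable to spontaneously expectorate".
- **Contamination.** In the FB-BAL section, "suction of secretions will be avoided before BAL to limit contamination with upper airway organisms".
- **Reason for looking beyond FB-BAL.** The Discussion reports that in CF-SPIT "some pathogens were isolated from induced sputum and not FB-BAL reflecting the relative inability of FB-BAL to sample the larger airways". It offers no such reason for organisms found only on a cough swab, and notes that a single swab did not represent lower-airway microbiology in CF.

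**The concern.** The reference, the scoring rule and the interpretation are all fixed in the article, so this is not a detail left to an analysis plan. Two features make the stated interpretation unsafe.

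First, every technique contributes to the reference it is judged against. Within this analysis no technique can be charged with a false positive, because whatever it grows is true by definition.

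Second, the throat swab has the same standing as the lower-airway samples. Upper-airway organisms are contamination to be limited when the bronchoscope is passed, but pathogens to be found when they come from the swab. A swab-only organism of that kind is scored as a miss for FB-BAL and for induced sputum.

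Sensitivity is the first-listed secondary outcome, and it will be read as evidence on whether swab or sputum can stand in for FB-BAL. Induced sputum, one of the two candidates, would be marked down for contamination of a different sample.

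**Working it through.** **1. The plan's own figures.** The sensitivity analysis has no stated target value. The sample size reproduces. With discordance 0.37 and ratio 3, d = 0.37 × (3 − 1)/(3 + 1) = 0.185. Then n = [1.96√0.37 + 1.2816√(0.37 − 0.185²)]² / 0.185² = 109.4, so 110, and 110/0.84 = 130.95, so 131. No input involves the composite reference.

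**2. CF-SPIT counts (Discussion).** The union held 39 pathogens: induced sputum found 27 (69%) and six-lobe FB-BAL 33 (85%). The overlap is 27 + 33 − 39 = 21. Sputum is therefore 27/39 = 69% against a union that contains it, and 21/33 = 64% against six-lobe FB-BAL. The 39 − 33 = 6 sputum-only pathogens may be real, so this gap is not all bias.

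**3. Mechanism, one-pathogen model.** Assume that 68% of children have one true pathogen (CF-SPIT: 28/41 with growth), that FB-BAL is perfect, that the swab finds 44% (the earlier CF study in the Discussion), and that a swab-only upper-airway organism occurs independently with probability f.

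- FB-BAL = 0.68(1 − f) / (0.68 + 0.32f)
- Swab = (0.68 × 0.44 + 0.32f) / (0.68 + 0.32f)

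| f | FB-BAL | Swab |
|---|---|---|
| 0 | 100% | 44% |
| 0.10 | 0.612/0.712 = 86% | 0.3312/0.712 = 46.5% |
| 0.20 | 0.544/0.744 = 73% | 0.3632/0.744 = 49% |
| 0.30 | 0.476/0.776 = 61% | 0.3952/0.776 = 51% |

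The two effects differ in size. FB-BAL loses in every child with a swab-only organism. The swab gains only from children with no other pathogen, who enter the denominator as swab successes. If every child had a true pathogen, then at f = 0.20 FB-BAL would fall to 80% and the swab would stay at 44%.

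**4. Illustration with several organisms.** Assume four organisms (the Introduction names four common ones), each truly present in 24% of children, so that 1 − 0.76⁴ = 67% have at least one. Per-organism detection is 95% for FB-BAL, 70% for sputum and 44% for swab. Throat carriage c per organism is independent and always picked up by the swab; the other two samples are uncontaminated.

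Let u be the probability that an organism is in the union, and m the probability that it is in the union but missed by the technique. The plan's sensitivity is then [(1 − m)⁴ − (1 − u)⁴] / [1 − (1 − u)⁴].

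For FB-BAL at c = 10%:
- the swab misses a true organism with probability 0.56 × 0.90 = 0.504
- u = 0.24(1 − 0.05 × 0.504 × 0.30) + 0.76 × 0.10 = 0.3142
- m = 0.24 × 0.05 × (1 − 0.504 × 0.30) + 0.76 × 0.10 = 0.0862
- sensitivity = (0.697 − 0.221)/(1 − 0.221) = 61%

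| Carriage per organism | 0% | 5% | 10% | 15% |
|---|---|---|---|---|
| FB-BAL, plan's reference | 94% | 75% | 61% | 50% |
| Induced sputum, plan's reference | 62% | 49% | 40% | 32% |
| Swab, plan's reference | 35% | 43% | 49% | 54% |
| FB-BAL, true organisms | 93% | 93% | 93% | 93% |
| Induced sputum, true organisms | 61% | 61% | 61% | 61% |
| Swab, true organisms | 34% | 37% | 39% | 42% |

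The swab's rise against true organisms comes from carried organisms that also happen to be present in the lower airway.

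**5. Reference without swab-only organisms** (FB-BAL plus induced sputum), same assumptions: FB-BAL 95%, induced sputum 62.5% and swab 34–42% across the carriage range. These are close to the true-organism values and, for FB-BAL and sputum, do not depend on carriage.

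**The case against.** **A composite is a reasoned choice.** PBB is described as infection of the conducting airways, the Discussion says FB-BAL samples the larger airways poorly, and six-lobe FB-BAL missed 6 of 39 CF-SPIT pathogens. The objectives also ask for FB-BAL's own sensitivity, which needs something wider than FB-BAL. This stands, and it is why the composite should be kept. It does not justify admitting swab-only organisms as lower-airway pathogens.

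**The size is assumed.** This stands too. Carriage of 15% for each of four independent organisms means that 1 − 0.85⁴ = 48% of children carry at least one, all detected by the swab. Sputum is assumed clean although oropharyngeal suction is allowed. Contaminated sputum would work in the other direction for the swab: in the one-pathogen model with f = 0, a 10% rate of sputum-only false positives lowers the swab from 44% to 38% and FB-BAL from 100% to 86%, and raises sputum from 69% to 70%.

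A reader might infer three stronger things, which the documents do not support:

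- *That the plan cannot reveal false positives.* The primary analysis classifies CS+/FB-BAL− separately, against one, two and six lobes, and does the same for induced sputum. At 15% carriage about 40% of children would fall in that cell. Only the secondary figure, read alone, hides them.
- *That the plan will rank the swab above FB-BAL.* In the illustration this happens only at the top of the assumed range. In the one-pathogen model it does not happen even at f = 0.30 (61% against 51%, or 53% against 52.5% if FB-BAL truly detects 85%).
- *That six-lobe FB-BAL should become the main reference.* That would set FB-BAL to 100% by construction and defeat a stated objective.

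The absence of specificity or predictive values is not a finding either, since a condensed article may leave these to the analysis plan.

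**Conclusion.** The concern holds for one secondary outcome. As written, the analysis gives relative pathogen yield among three samples, not sensitivity for lower-airway pathogens. If some swab-only organisms come from the upper airway, the figures for FB-BAL and induced sputum are too low; this is the larger and more certain effect. The swab's figure is too high only to the extent that such organisms appear in children with no other pathogen.

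The direction follows from the definitions. The size does not: it rests on a carriage rate absent from the documents, on CF figures used as stand-ins, and on independence between samples. At an assumed 10% per organism, FB-BAL would read 61% rather than about 93%, and induced sputum 40% rather than about 61%. The primary analysis and the sample size of 131 stand.

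**What to change.** 1. Label the triplicate-composite result as relative pathogen yield that includes the index test, and drop the claim that it measures sensitivity for lower-airway pathogens.
2. Add a prespecified sensitivity analysis whose reference omits swab-only organisms, that is, FB-BAL plus induced sputum. State that FB-BAL and sputum are still each part of this reference.
3. Report cough swab and induced sputum against six-lobe FB-BAL as a supplementary comparison. It does not depend on whether sputum collected by suction is clean.
4. Give score confidence intervals for all of these, as already planned for sensitivity.

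The cost is wording and a few extra analyses of data already collected, with no new samples, visits or recruitment. The downside is that a true lower-airway organism found only on the swab would be left out of the added reference, which is why the composite stays alongside it.

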### Study oversight and monitoring

#### Trial management group

The trial management group will be responsible for the day-to-day management of the study. It will consist of the chief investigator (CI), principal investigators, statistician, clinical trial manager, data manager, data co-ordinator, qualityassurance manager and microbiology lead.

#### Trial Steering Committee

The TSC will provide supervision for the trial/study on behalf of the sponsor and funder. It will also provide expert advice independent of the CI and the Sponsor. The TSC will consist of an independent chair, two independent paediatric respiratory consultants, an independent statistician, the PPIE lead and the CI.

#### Study monitoring

Monitoring will be undertaken in accordance with the study monitoring plan. The monitor may review processes related to participant enrolment, eligibility, consent and adherence. They will also assess policies to protect participants, including reporting of harm and completeness, accuracy and timeliness of data collection. Monitoring may be carried out remotely by exploring the study dataset or performing site visits.

#### Data management

Data will be collected in accordance with the data management plan using CRFs. The completed CRFs will be returned to the data coordinator and inputted onto the REDCap database. Data quality checks will be conducted periodically to ensure accuracy of the primary and secondary outcomes.

#### Study progress

This 24 month trial opened on 01/10/2021. Recruitment started on 01/01/2022 and will be open for 17 months.

## Discussion

CLASSIC PBB will compare the pathogen yield from different lower airway sampling strategies in children with PBB. If either cough swab or induced sputum are shown to be useful alternatives to FB-BAL, it will enable more children with PBB to have the causative pathogen identified and therefore be prescribed targeted antibiotics. It would also reduce the need for FB-BAL in this condition which would be beneficial to children and their families due to the associated burden.

Cough swabs and induced sputum samples are not used routinely in children with PBB. They are, however, widely used in children with other respiratory illnesses who are unable to expectorate sputum. At UK paediatric CF) Centres, a cough swab is obtained at each out-patient appointment (2–3 monthly) as part of routine microbiological surveillance.^17^ They are easy to perform and well tolerated. The CF-SPIT study compared pathogen yield from cough swab, induced sputum and FB-BAL samples in children aged 6 months to 18 years with CF. They reported 69% of pathogens isolated at FB-BAL had been identified in cough swabs over the previous 12 months but a single cough swab was not representative of lower airway microbiology in CF. This supports the findings of a previous study which found the sensitivity of a single cough swabs to be 44% when compared with FB-BAL samples.^18^

Induced sputum has been shown to be a simple, cost effective, well tolerated and repeatable method of sampling the lower airway in children with CF.^15 19^ In the CF-SPIT study, the pathogen yield of 41 paired induced sputum and FB-BAL samples was compared.^15^ Of the 41 paired samples, 28 (68%) had a positive growth from at least one of the samples with 39 pathogens isolated in total. Induced sputum identified 27 (69%) pathogens, single-lobe FB-BAL identified 22 (56%), two-lobe FB-BAL 28 (72%) and six-lobe FB-BAL identified 33 (85%). Importantly, some pathogens were isolated from induced sputum and not FB-BAL reflecting the relative inability of FB-BAL to sample the larger airways. The authors of the CF-SPIT concluded that in children with CF, sputum induction is a credible surrogate for BAL and a substantial number of FB-BALs could be avoided if sputum induction is done first and pathogens appropriately treated.^15^

Although induced sputum sounds unpleasant, the success and tolerability rates in published cohorts is high. The three largest cohorts (CF-SPIT^15^ and two studies of children with suspected TB^20 21^ report 1099 attempts at induced sputum in 523 children aged 1 month to 16 years. A sputum sample was successfully obtained in 94% of procedures. Objective tolerance of the sputum induction procedure is good with CF-SPIT reporting no significant effects on respiratory rate, heart rate, or FEV_1_%. Subjective tolerance was also good. Likert scales rated tolerance high, with mean parent or patient scores of 8·55 (SD 1·65) and physiotherapist scores of 9·09 (1·76). During the 200 induced sputum reported in CF-SPIT, there was a low incidence of side-effects: 17 (9%) became upset, of which four (2%) could not complete the procedure; six (3%) had mild wheeze, of which two (1%) could not complete the procedure; three (2%) patients vomited during oropharyngeal suction and one (<1%) became transiently dizzy.

While induced sputum has been shown to be a useful alternative to FB-BAL in children with CF and TB it cannot be assumed this is the case for PBB. Children with PBB are younger than those with CF and the respiratory pathology is less suppurative. These factors potentially affect the likelihood of successfully obtaining samples.

## Data Availability

No data are available.
